### Study design

This is an open-label phase II multi-centre randomized trial. Patients will be randomized between current standard of care treatment (Arm 1) vs. omission of radiation to the pN0 dissected hemi-neck(s) (Arm 2) in a 1:2 ratio (Fig. 1). The required sample size is 90 patients. Stratification factors include neck nodal status (pN0 vs pN+) and use of chemotherapy. Patients will be recruited from tertiary care centres (full list of participating sites available on clinicaltrials.gov, NCT03997643).

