If randomized to omission of PORT to pN0 neck (Arm 2), the CTVn60neg and CTV54neg contours are deleted after randomization, prior to treatment planning. To prevent bias, contours cannot be changed after randomization. Local peer review of contours must take place before randomization occurs. An overview of the protocol timeline is shown in Fig. 3.

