#### Statistical considerations

##### Sample size

The primary endpoint is the rate of relapse in the pN0 neck (i.e. the regional relapse rate in the pN0 neck) in Arm 2, compared to historical controls. All other endpoints are a comparison between Arm 1 and Arm 2.

It is generally accepted that a risk of nodal recurrence of 15–20% is sufficient to warrant radiation to a nodal basin, and therefore we wish to exclude a risk of regional recurrence in the pN0 neck of 20% at 2-years. Using a one-sided, one-sample binomial test, allowing for 5% dropout, a sample size in Arm 2 of 60 patients provides 83.1% power at a 0.05 significance level to detect a regional control rate in the pN0 neck of 92%, compared to an unacceptable level of 80%.

This sample size (30 in Arm 1 and 60 in Arm 2) also allows for > 80% power to detect a 10-point difference in the total MDADI score at 1 year (a secondary endpoint), assuming the scores are normally distributed with a standard deviation of 15 in each arm. It is generally believed that a 10-point difference in standardized QoL scores represents a clinically significant difference in QoL [42]. It is assumed that the QoL scores will be normally distributed with a standard deviation of 15 in each arm. The MDADI will be calculated as the composite score, but will also be reported for each of the subscales.

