#### Analysis plan

Patients will be analyzed in the groups to which they are assigned (intention-to-treat). Oncologic outcomes and OS will be calculated from date of randomization using the Kaplan-Meier method. A one-sided, one-sample binomial test will be used for the primary endpoint as described above. For actuarial comparisons between arms, the stratified log-rank test will be used (stratified by stratification factors). An two-sample T-test will be used to compare QoL scores at 1-year. The percentage of patients in each arm who experience a clinically significant QoL decline on the MDADI (10 points) will also be reported.

MBSImP™© scores will be compared at 1-year, including the total score, and the scores on the oral and pharyngeal subscales, using a two-sample T-test or a Wilcoxon rank sum test as appropriate. DIGEST™ and FOIS scores will be compared using the Chi-square test.

Pre-planned subgroup analysis will occur based on the stratification variables (nodal status [pN0 vs. pN+] and use of concurrent chemotherapy), as well as based on the neck dissection performed (unilateral vs. bilateral), and T-stage (T1–2 vs. T3–4). There will also be a pre-planned analysis based on the extent of nodes harvested in the pN0 neck (< 18 vs. 18 or more), depth of invasion of the primary tumour (< 4 mm vs. 4 mm or more), and photon versus proton treatment.

Multivariable Cox proportional hazards or logistic regression analysis, as appropriate, will be used to determine baseline and pathologic factors predictive of pN0 neck failure, DFS, OS, locoregional recurrence and salvage therapy. For the secondary endpoints involving QoL scales, linear mixed effects models will be used; for the MDADI, the total scores will be compared between the two arms, whereas for the EORTC QLQ-C30 and H&N35 scales, each of the subscales (e.g. pain, swallowing, etc.) will be compared between the two arms.

Rates of grade ≥ 2 toxicity and use of feeding tubes will be compared between arms using the Chi-square or Fisher’s exact test, as appropriate.

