Utilities will be calculated from the EQ-5D-5L which will be administered at baseline and at 6 month intervals. Quality adjusted life years (QALYs) will be assessed as the area under the preference-weighted survival curve. Overall costs of each treatment strategy will be abstracted from the available literature. The incremental cost effectiveness ratios (ICERs) between treatment arms will be compared through the standard method of ratio between differences in costs and QALYs. Point estimates for these differences can be derived from multivariable generalized estimating equations (GEE) or generalized linear model (GLM) analyses.

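### Baseline quality-of-life scores need only precede radiotherapy, not randomization, so in this open-label trial the MDADI decline rates and the QALY starting point may use a baseline scored after the patient knows the arm

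*Protocol article*

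**What the plan says.** All references are to the protocol article.

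- **Baseline timing.** The Pre-treatment evaluation list uses two anchors. The history and physical, staging imaging, pregnancy test and contour peer review are tied to randomization. Quality-of-life scoring and the baseline barium swallow need only come before treatment begins, and the dysphagia grade is due within two weeks of treatment start. The list does not name the questionnaires. Secondary endpoints gives them as MDADI, QLQ-C30, H&N35, EQ-5D-5L and NDII.
- **Blinding.** Study design: "This is an open-label phase II multi-centre randomized trial".
- **Order of events.** Contours are finalized, then the patient is randomized. In Arm 2 the node-negative neck "contours are deleted after randomization, prior to treatment planning" (Clinical Target Volumes).
- **Analyses that may use baseline.** The Analysis plan states: "The percentage of patients in each arm who experience a clinically significant QoL decline on the MDADI (10 points) will also be reported". It also says "For the secondary endpoints involving QoL scales, linear mixed effects models will be used", without stating the role of baseline. For the QALYs, "Utilities will be calculated from the EQ-5D-5L which will be administered at baseline and at 6 month intervals".
- **Analyses that do not.** "An two-sample T-test will be used to compare QoL scores at 1-year". The MBSImP scores are likewise compared at 1 year, and DIGEST and FOIS, which are 1-year endpoints, by Chi-square test.

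**The concern.** A self-reported score taken after the patient has learned the arm can already respond to that knowledge. Relief or worry about leaving the neck unirradiated could move it, in either direction, before any radiation is given. Any analysis that treats such a score as the pre-treatment reference may then show a between-arm difference that treatment did not cause, or hide one that it did.

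The protocol recognises this kind of risk for contours, which it freezes at randomization to prevent bias. The more subjective patient-reported baseline has no such protection. A later analysis plan could define baseline as the last pre-randomization value, but it cannot recover a value that was never collected. The rule therefore belongs in the protocol's assessment list.

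**Working it through.** **1. Can a post-allocation baseline occur under the plan?** Yes. Planning follows randomization, so every patient has an interval between allocation and first fraction. Its length is not given. Baseline scoring is allowed anywhere before treatment starts, and patients are not blinded. No section at hand requires the questionnaires before allocation; the follow-up schedule in Additional file 2 is not shown.

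**2. The plan's own quality-of-life figure.** Sample size states that 30 and 60 patients "also allows for > 80% power to detect a 10-point difference in the total MDADI score at 1 year", with SD 15. Taking a two-sided 5% test (the sidedness is not stated for this comparison):

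- SE = 15 × √(1/30 + 1/60) = 3.354
- power ≈ Φ(10/3.354 − 1.96) = Φ(1.02) ≈ 84.6%; with the t distribution, 83.9%
- with 28 and 57 patients, after about 5% dropout, 81.5% (t distribution)

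The stated figure reproduces. It uses 1-year scores only, so baseline timing does not enter.

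**3. MDADI decline rate (illustration).** From the plan: SD 15 and a 10-point threshold. Assumed: normal scores, baseline-to-1-year correlation r = 0.5, mean change 0, no true arm effect, and a baseline raised by s points in one arm with no carry-over to 1 year.

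- SD of change = 15 × √(2(1 − r)) = 15
- P(decline ≥ 10) = Φ((−10 + s)/15)

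| Shift s | Calculation | Decline rate |
|---|---|---|
| 0 | Φ(−0.667) | 25.2% |
| 2 | Φ(−0.533) | 29.7% |
| 3 | Φ(−0.467) | 32.0% |
| 5 | Φ(−0.333) | 36.9% |

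Downward shifts of 2 and 5 points give 21.1% and 15.8%. With r from 0.3 to 0.7 and a mean change of 0, −5 or −10, an upward shift of 2 points adds about 4 to 7 percentage points, and one of 5 points adds about 10 to 17.

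**4. QALYs (illustration).** Assumed: linear interpolation between utility measurements and a baseline utility shift of 0.03–0.05. If the next measurement is at 6 months:

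- 0.5 × 0.5 year × 0.03 = 0.0075
- 0.5 × 0.5 year × 0.05 = 0.0125

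Secondary endpoints also lists EQ-5D-5L at treatment completion. Thirty fractions take about 6 weeks (0.12 year). If that measurement is used, the effect falls to 0.5 × 0.12 × 0.03 to 0.05 = about 0.002–0.003.

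**5. Mixed models (conditional).** If baseline is a covariate, the false arm effect is about r × s. At r = 0.5 this is 1.0 point for s = 2 and 2.5 points for s = 5. If baseline does not enter the model, the effect is nil. The plan does not say which applies.

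**The case against.** **The comparisons that matter most use no baseline.** This stands in full. The primary endpoint is pN0 neck failure in Arm 2. The powered MDADI test and the 1-year MBSImP, DIGEST and FOIS comparisons use follow-up scores only. No stated comparison uses a baseline swallow study or dysphagia grade. The MDADI decline rate is to be reported, with no test named.

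**A reader might infer that the type I error of the quality-of-life analysis is inflated.** The documents do not support that. An inflated error rate would need a baseline-adjusted or change-score test, and the Analysis plan specifies neither. Baseline is also absent from the longitudinal time points in Secondary endpoints, so its place in the mixed models is open.

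**The illustration assumes that knowing the arm shifts baseline but not the 1-year score.** This is fair, because later scores are open-label too. If the same shift persisted unchanged to 1 year, it would cancel from a change measured against a post-allocation baseline. In a covariate-adjusted model with r = 0.5 and a 5-point shift, the bias would then be (1 − 0.5) × 5 = 2.5 points with a post-allocation baseline and 5 points with an earlier one. The illustration therefore cannot be read as a forecast. But exact cancellation is itself an undocumented assumption, and it is no reason to take a reference score after allocation.

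**A baseline close to treatment better reflects the patient's state before radiation, given postoperative recovery.** This has some weight. The questionnaires need move only across the planning interval, however, so the loss is small.

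**Conclusion.** The point holds within limits. The protocol permits, but does not require, a self-reported baseline scored after the patient knows the arm. Nothing shows how often that would happen. Exposed are the reported MDADI decline rates (taking baseline as their reference), the starting utility of the QALY curve, and the mixed models if baseline enters them. All are secondary analyses.

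The MDADI illustration shows a possible false difference of roughly 4 to 17 percentage points for assumed shifts of 2 to 5 points. The QALY effect is small, at most about 0.0125 under the stated assumptions. Only the SD of 15 and the 10-point threshold come from the protocol. The shifts, correlations, mean changes and absence of carry-over are assumptions, and the direction is unknown.

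A reader might take this as a threat to the primary result, to the powered quality-of-life comparison or to the swallowing results; the planned analyses rule that out as far as baseline timing goes. This is a cheap improvement, not a flaw in the main design.

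**What to change.** In Pre-treatment evaluation, require all quality-of-life questionnaires (MDADI, QLQ-C30, H&N35, EQ-5D-5L, NDII) before randomization, or at the least before the allocation is disclosed, and as close to it as practical. In the Analysis plan, use that score as baseline for the MDADI decline, for the QALYs and, where baseline enters, for the mixed models.

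For patients already enrolled, record whether each baseline preceded allocation, and repeat the baseline-dependent analyses without the post-allocation ones.

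Moving the barium swallow, FOIS and dysphagia grade in the same way is optional, because no stated comparison uses their baseline.

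The cost is a small change to the assessment schedule. Questionnaires are completed slightly earlier in postoperative recovery, and a few patients will complete them without being randomized. Sample size and stated power do not change.

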#### Secondary endpoints

OSDisease-free survival (DFS)Local recurrenceRegional recurrenceLocoregional recurrenceRate of salvage treatment (surgery ± radiotherapy) in the pN0 neck, and freedom from unsalvageable neck recurrenceQoL at 1 year, assessed with the MD Anderson Dysphagia Inventory (MDADI) [28], the European Organisation for Research and Treatment of Cancer (EORTC) Quality of Life Cancer Patients general (QLQ-C30) [29] and head & neck (H&N35) scales [30], the EuroQOL 5-Dimension 5-Level (EQ-5D-5L) [31], and the Neck Dissection Impairment Index (NDII) [32]QoL measured at treatment completion and 6, 12, 15,18, 24, 30, 36, 42, 48, 54 and 60 months, measured with MDADI, EORTC QLQ-C30, H&N35, EQ-5D-5L and NDIIRate of feeding tube insertion after start of radiation (either gastric, gastrojejeunal, or nasogastric) and rate of feeding tube use at 1-year post-randomization.Swallowing function at 1-year, assessed by Modified Barium Swallow (MBS) study and measured by the Modified Barium Swallow Impairment Profile (MBSImP™©) score [33], the Dynamic Imaging Grade of Swallowing Toxicity (DIGEST™) score [34], and the Functional Oral Intake Scale (FOIS) [35].Toxicity, assessed using the National Cancer Institute Common Toxicity Criteria (NCI-CTC) version 4.03Rate of failure in the clinically node negative neck, if applicable (i.e. the undissected node-negative neck, for well-lateralized tumours).

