#### Enrollment, randomization and allocation

Patients will be enrolled by dedicated clinical trials staff and/or the investigator at each participating institution. Patients will randomized in a 1:2 ratio to standard radiation volumes (Arm 1) vs omission to the pN0 neck (Arm 2). A permuted block design with two stratification factors will used with the size of the blocks known only to the statistician, stratified based upon overall neck nodal status (pN0 vs. pN+) and use of concurrent chemotherapy (yes vs. no). Randomization sequences are generated for each strata separately with a random number generator based on permuted block design. This gets formatted as a CVS file which gets uploaded into REDCap [41].

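### DIGEST and FOIS, two ordered swallowing scales, are to be compared by a Chi-square test that ignores their order; under a consistent shift this gives up roughly 10 to 25 points of power on secondary endpoints

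*Protocol article*

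**What the plan says.** The Secondary endpoints section lists "Swallowing function at 1-year, assessed by Modified Barium Swallow (MBS) study" and measured by three instruments: MBSImP, "the Dynamic Imaging Grade of Swallowing Toxicity (DIGEST™) score" and FOIS. By name, DIGEST is a grade and FOIS a functional scale, so both are ordered.

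The Analysis plan gives MBSImP a t-test or a Wilcoxon rank sum test. The next sentence says that DIGEST and "FOIS scores will be compared using the Chi-square test". It describes no grouping of levels and offers no rank or trend alternative. Later in the same section, toxicity and feeding-tube rates may be compared by Chi-square or Fisher's exact test.

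The Sample size section sets 30 patients in Arm 1 and 60 in Arm 2. It gives power for the primary endpoint and for the MDADI, and none for DIGEST or FOIS. Pre-treatment evaluation has both scores documented at baseline.

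**The concern.** A Pearson Chi-square test on an arm-by-level table treats the levels as labels. A steady move towards better swallowing is spread over as many degrees of freedom as there are levels minus one, and the test yields no single measure of direction or size.

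A steady move is the pattern the trial's reasoning points to. The experimental arm irradiates less tissue, and the Data safety monitoring committee section calls higher toxicity in that arm extremely unlikely. In a 90-patient trial meant to inform phase III design, a non-significant Chi-square result on DIGEST or FOIS could be read as no functional difference when the test was simply weak against the expected one.

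**Working it through.** **The plan's own figures.** None is stated for DIGEST or FOIS. The primary calculation reproduces: "allowing for 5% dropout" takes Arm 2 from 60 to 0.95 × 60 = 57. Calling it a success when at least 51 are controlled gives P(X ≥ 51 | 0.80) = 0.0451 and P(X ≥ 51 | 0.92) = 0.831, the stated 83.1%. The arm sizes can therefore be taken at face value.

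**Inputs.** From the article: 30 vs 60, analysed at 1 year. Assumed, because the article does not say: two-sided 0.05; five DIGEST levels with Arm 1 proportions 0.30, 0.35, 0.20, 0.10, 0.05 (best to worst); seven FOIS levels with Arm 1 proportions 0.04, 0.04, 0.05, 0.10, 0.22, 0.25, 0.30 (worst to best); and a proportional-odds shift towards better scores in Arm 2.

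**Why power is lost, by formula (five levels, odds ratio 2.5).** Multiplying the Arm 1 cumulative odds by 2.5 gives Arm 2 proportions 0.517, 0.306, 0.111, 0.045, 0.021. The pooled proportions p̄ are 0.445, 0.320, 0.141, 0.064, 0.030.
- Chi-square noncentrality = (n₁n₂/N) Σ(p₂ − p₁)²/p̄ = 20 × 0.2436 = 4.87 on 4 df. Power is about 39%.
- Rank test noncentrality = (ln OR)² × V, with V = n₁n₂N/[3(N + 1)²] × (1 − Σp̄³) = 162,000/24,843 × (1 − 0.124) = 5.71. Then 0.8396 × 5.71 = 4.80 on 1 df. Power is about 59%.

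The two tests see nearly the same signal, but the Chi-square test spreads it over 4 df. For seven levels the values are 4.99 on 6 df (about 34%) and 4.89 on 1 df (about 60%).

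**Simulation** (20,000 trials per row, 30 vs 60, Pearson Chi-square with empty levels dropped, tie-corrected Wilcoxon):

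| Levels | Odds ratio | Chi-square | Wilcoxon | Gap (points) |
|---|---|---|---|---|
| 5 | 2.0 | 25.9% | 39.5% | 13.6 |
| 5 | 2.5 | 41.9% | 60.1% | 18.2 |
| 5 | 3.0 | 56.8% | 75.4% | 18.6 |
| 7 | 2.0 | 23.8% | 40.9% | 17.1 |
| 7 | 2.5 | 38.6% | 60.5% | 21.9 |
| 7 | 3.0 | 52.5% | 75.9% | 23.4 |

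At 28 vs 57 (about 5% dropout in both arms) and odds ratio 2.5, the gaps are 17.2 and 22.2 points.

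**Other assumed shapes** (30 vs 60, odds ratios 2 to 3). Five levels: 10 to 16 points if very skewed, 16 to 20 if flat. Seven levels: 14 to 21 if very skewed, 20 to 27 if flat. Only four levels in use: 10 to 14. Extending to odds ratio 4 and to arms of 24 vs 48, the full range is about 8 to 27.

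**Sparse cells.** With no difference between arms, expected DIGEST counts are 9, 10.5, 6, 3, 1.5 in Arm 1 and 18, 21, 12, 6, 3 in Arm 2, so 3 of 10 cells fall below 5. For FOIS they are 1.2, 1.2, 1.5, 3, 6.6, 7.5, 9 and 2.4, 2.4, 3, 6, 13.2, 15, 18, so 7 of 14 fall below 5. Even so, simulated type I error of the Chi-square test at 30 vs 60 is 0.037 to 0.048 over the shapes tried.

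**The case against.** **The size is not in the document.** Levels, distributions and shift are all assumed. This stands. Any single figure for the loss would be a product of the assumptions, so only a range is given.

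**The test may be meant for grouped scores.** If each scale were cut into two categories, the tests would agree: for 30% vs 10% at 30 vs 60 both have 67% power. A condensed article may leave grouping to a fuller document. But the sentence speaks of scores and fixes the test, and the neighbouring sentence shows that rank tests were considered for a similar measure.

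**A rank test is not always better.** In one crossing pattern that was simulated, Chi-square had 70% power and Wilcoxon 11%. This stands as the cost of the change. Nothing in the trial's rationale predicts crossing, and a table of level counts would show it.

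**The domain is already covered.** MBSImP is compared by tests that use order, and the MDADI is the powered secondary endpoint. This limits the consequence without justifying the weaker test here.

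**Inferences to avoid.** A reader might infer from the sparse cells that the p-value cannot be trusted. The simulated error rate stays at or below 0.05, so the cost is power and not false positives. A reader might also treat the missing exact-test fallback, or the lack of baseline adjustment, as errors. Both are details that a protocol article may leave to an analysis plan, and the article does not say that baseline scores will be ignored. Nor does it hypothesise better swallowing function: the stated hypothesis concerns regional recurrence and quality of life, and function is to be assessed.

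**Conclusion.** The point holds as a stated choice of a weaker test. The Chi-square test ignores the order of DIGEST and FOIS, while the same paragraph allows a rank test for MBSImP. Assuming five to seven levels, 30 vs 60 patients and a consistent shift, it gives up roughly 10 to 25 points of power, and about 8 to 27 over everything tried.

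The consequence is limited to two measures within the secondary endpoints. Neither was powered, and in the tabulated scenarios even the rank test stays below 80%. The change is worth making because it costs almost nothing, but it does not bear on the trial's main conclusion.

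**What to change.** Replace the sentence with one pre-specified rank test for both scales at 1 year: either the tie-corrected Wilcoxon rank sum test, or the van Elteren test stratified by nodal status and chemotherapy. Choose between them before any comparison by arm is seen. Do not make the choice depend on whether a model fits, since that would let the data select the test. The power figures above are for the unstratified Wilcoxon; van Elteren was not simulated.

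Show the number of patients at each level by arm. As a supportive estimate, report the common odds ratio with its 95% interval from a proportional-odds model, adjusted for the baseline score already collected where the data allow. This model informs the size of the effect and does not replace the test.

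The cost is analysis wording only, with no added patients, visits or data. The drawback is lower power than Chi-square against a crossing difference, which the level counts would bring to light.

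### Grade ≥2 toxicity and feeding-tube use are compared without the randomization strata: valid, but conservative to the extent that the strata predict these outcomes

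*Protocol article*

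**What the plan says.** Under Enrollment, randomization and allocation, patients are "randomized in a 1:2 ratio to standard radiation volumes (Arm 1) vs omission to the pN0 neck (Arm 2"), "stratified based upon overall neck nodal status (pN0 vs. pN+) and use of concurrent chemotherapy (yes vs. no"). The blocking is done within each stratum: "Randomization sequences are generated for each strata separately with a random number generator based on permuted block design". Two binary factors give four strata.

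Under Analysis plan, for time-to-event comparisons between arms, "the stratified log-rank test will be used (stratified by stratification factors"). For grade ≥2 toxicity and feeding tubes the strata disappear: rates of the former and "use of feeding tubes will be compared between arms using the Chi-square or" Fisher's exact test, as appropriate. The multivariable Cox or logistic models in that section cover pN0 neck failure, DFS, OS, locoregional recurrence and salvage therapy. They do not cover toxicity or feeding tubes.

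Both outcomes are listed under Secondary endpoints. The power statements under Sample size concern the single-arm primary endpoint and the 1-year MDADI score only.

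**The concern.** Stratified blocking makes the arms nearly balanced on nodal status and chemotherapy. If these factors predict the outcome, the difference between arms varies less from trial to trial than under simple randomization. A pooled test does not use this: its variance still includes the variation between strata. Its actual type I error then falls below nominal, and it loses power.

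Both factors could plausibly matter here. The Background links larger irradiated volumes to more toxicity, and in Arm 2 a pN+ patient keeps the involved hemi-neck in the target volume while a pN0 patient does not. Treatment plan ties chemotherapy to patients able to tolerate it.

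Comparing toxicity between arms is a stated objective, and only 30 and 60 patients are available. For feeding tubes the number is smaller still, because patients with a tube placed before randomization are censored. At stake is some avoidable risk of missing a real reduction in toxicity or tube use.

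**Working it through.** **1. The plan's own figures.** For the primary test, n = 60 × 0.95 = 57. The smallest number of controlled necks with exact P(X ≥ c | 57, 0.80) ≤ 0.05 is c = 51, giving α = 0.0451. Power is P(X ≥ 51 | 57, 0.92) = 83.13%, against 83.1% stated. For the MDADI (10 points, SD 15, 30 vs 60, two-sided 0.05 assumed), the t-test has 83.9% power, or 81.5% with 28 vs 57 patients, against more than 80% stated. Both reproduce. There is no stated figure to reproduce for toxicity or feeding tubes.

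**2. Why the pooled test is conservative.** Let stratum s have share w_s and event rate p_s under no treatment effect, and let p̄ = Σ w_s p_s. With balance within strata, the variance of the difference is proportional to Σ w_s p_s(1 − p_s), whereas the pooled Chi-square uses p̄(1 − p̄). With r the ratio of the first to the second, the actual two-sided level is about 2[1 − Φ(1.96/√r)].

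Example, with assumed shares 35/15/20/30% and rates 25/60/40/85% (strong strata):
- p̄ = 0.0875 + 0.09 + 0.08 + 0.255 = 0.5125, so p̄(1 − p̄) = 0.2498
- Σ w_s p_s(1 − p_s) = 0.0656 + 0.0360 + 0.0480 + 0.0383 = 0.1879
- r = 0.752, 1.96/√r = 2.260, level about 2.4%

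With moderate strata (40/60/50/75%), p̄ = 0.555 and r = 0.2262/0.2470 = 0.916, so the level is about 4.1%. With equal rates r = 1 and nothing is lost.

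**3. Simulation A.** 10,000 trials per scenario, N = 90, 1:2 blocks of 6 within four strata, the shares above, two-sided 0.05, CMH without continuity correction. Power is at a within-stratum log odds ratio of −1.0. Shares, block size, rates and effect are all assumptions, because the article gives none of them.

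| Arm 1 rates across strata | Type I error, Chi-square / CMH | Power, Chi-square / CMH | Loss (points) |
|---|---|---|---|
| 60% in all | 5.5 / 5.4% | 61.0 / 60.3% | none |
| 50–70% (mild) | 4.8 / 4.9% | 58.0 / 58.6% | 0.6 |
| 40–75% (moderate) | 4.0 / 4.6% | 53.3 / 56.0% | 2.7 |
| 25–85% (strong) | 2.7 / 5.4% | 36.1 / 47.2% | 11.1 |
| Tube-like, 10–40% | 4.2 / 4.9% | 37.0 / 38.6% | 1.6 |
| Tube-like, 5–55% | 2.5 / 5.1% | 30.8 / 37.1% | 6.3 |
| 10–90% (extreme) | 0.5 / 4.4% | 10.5 / 31.0% | 20.5 |

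The levels agree with step 2 (4.0% against 4.1%, and 2.7% against 2.4%). The Monte Carlo standard error is about 0.2 points for the level and 0.5 for power.

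**4. Simulation B, other assumptions.** 20,000 trials per scenario, shares 30/15/25/30%, odds ratio 0.30. Chi-square against CMH power:
- weak (50/40/40/30%): 66.8 vs 66.8%, loss 0
- moderate (65/55/30/20%): 59.6 vs 63.4%, loss 3.8
- strong (75/65/30/20%): 53.9 vs 62.1%, loss 8.2
- very strong (85/75/25/15%): 36.1 vs 53.5%, loss 17.4

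A repeat of the first three gave 66.1 vs 66.2%, 58.6 vs 62.5% and 53.1 vs 61.2%.

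**5. Fisher and the form of the stratified test.** In simulation A with no stratum effect, Fisher's level is already 4.3% against 5.5% for Chi-square. In simulation B with weak strata its power is 60.9% against 66.8%. That gap is discreteness, not ignored strata. A further run of the simulation B setup (4,000 trials) included the exact CMH test:

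| Strata | Chi-square | Fisher | CMH, uncorrected | CMH, exact |
|---|---|---|---|---|
| Weak | 66.4% | 60.4% | 66.3% | 61.4% |
| Moderate | 60.0% | 53.4% | 63.8% | 58.5% |
| Strong | 53.8% | 47.9% | 62.2% | 55.8% |
| Low rates (30/25/12/8%) | 39.4% | 33.0% | 40.6% | 33.8% |

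Like for like, exact CMH gains about 1, 5, 8 and 1 points over Fisher. It has less power than the plain Chi-square in the weak, moderate and low-rate cases. A continuity-corrected CMH also does worse than Chi-square in simulation A's moderate case (46.3% vs 53.3%).

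**The case against.** The strongest reply is that this is a preference about efficiency. The endpoints are secondary, and the primary comparison is single-arm: "The primary endpoint is the rate of relapse in the pN0 neck (i.e. the regional relapse rate in the pN0 neck) in Arm 2". The powered between-arm comparison is the MDADI. The Analysis plan also uses plain tests for 1-year QoL, MBSImP, DIGEST and FOIS, so stratifying only the log-rank test is a consistent convention and not a contradiction. Even with CMH, power at an assumed odds ratio of 0.30 is only about 53 to 67% in simulation B. Adjusted analyses may also stand in an analysis plan that is not shown.

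Most of this stands, and it limits the point to an improvement. The last part does not remove it, because the article itself names the test for these two endpoints, and a plan that follows the article inherits that choice.

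A reader might infer two stronger things:
- **That the tests are too conservative as such, or that the p-values are wrong.** The documents do not support this. They give no toxicity or tube rates, none by stratum, no chemotherapy share and no block size, and with weak strata nothing is lost. Any departure is towards a level below nominal, so a false claim of benefit does not become more likely.
- **That stratification recovers the whole gap to Fisher's test.** It does not. Much of that gap is discreteness, and an exact stratified test shares it.

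**Conclusion.** The point holds in conditional form. The comparisons of grade ≥2 toxicity and feeding-tube use leave out factors that the design blocks on and that the log-rank tests use. The tests stay valid but are conservative to the extent that the strata predict the outcome.

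The loss of Chi-square against an uncorrected CMH test is about 0 points with weak strata, roughly 2 to 4 with moderate and 6 to 11 with strong. The losses of about 17 to 20 points appear only in extreme scenarios. All these sizes rest on assumed stratum shares, event rates, block size and odds ratios; the direction rests only on stratified blocking and prognostic strata. This is a matter of efficiency and consistency. It alters no stated figure and not the primary conclusion.

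**What to change.** In Analysis plan, before any unblinded comparison:
- Make the main test for grade ≥2 toxicity and feeding-tube use a CMH test **without continuity correction**, stratified by nodal status and concurrent chemotherapy as recorded at randomization. Logistic regression adjusted for both factors is an alternative.
- Report a stratified risk difference or common odds ratio.
- Keep the unstratified Chi-square or Fisher test as a sensitivity analysis.
- Where cells are sparse, allow an exact stratified test, and state that it can have less power than the plain Chi-square.

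The cost is wording only. The strata are already in the randomization record, and no new data or patients are needed. In the simulations the uncorrected test gave up less than 1 point when the strata did not matter (60.3% vs 61.0%).
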